### 5.6. Data Management

In this study, data registration will be performed prospectively in the electronic health records (EHRs) of all participating centers, according to a predefined and standardized set of variables. This prospective registration strategy is intended to minimize missing data and ensure uniformity across centers. At several predefined time points during the study period, data will be retrospectively extracted from the EHRs by the executive researcher, who will receive a guest appointment in each of the seven participating centers. If interim quality checks indicate incomplete or inconsistent registration in certain centers, feedback will be provided to optimize data quality during the ongoing study. Thus, while data registration is prospective, data collection for analysis will take place multiple times retrospectively during the inclusion period.

All data will be collected using a standardized protocol and entered into REDCap, in accordance with the FAIR principles (Findable, Accessible, Interoperable, and Reusable) [55]. All data will be securely and confidentially stored on the research network drive of the trauma division at the coordinating study center. Directly identifiable data (e.g., patient ID) will be stored separately in a password-protected Excel file, while research data will be pseudonymized and stored in REDCap, and exported to RStudio (version 2024.04.1, Posit, PBC) for statistical analysis only [56]. A coded key file will enable linkage between the datasets and will be securely stored separately. Only the principal investigator and executive researcher will have access to these files.

Data management procedures will adhere to the European Union General Data Protection Regulation (GDPR) and the Dutch Act on Implementation of the GDPR [57,58]. All data will be retained for 15 years following the end of the study, in line with ethical and legal requirements. The coordinating study center serves as the data controller and is responsible for safeguarding data integrity and security throughout the study period.

### 5.7. Sample Size and Rationale for Non-Inferiority

The research question of this study is framed as a non-inferiority comparison, and the sample size has therefore been calculated to test non-inferiority. This study used the most recent institutional data, as these best reflect the clinical context and patient population of this study. These institutional data showed a transfusion rate of approximately 15% in the delayed surgery group and 10% in the early surgery group, which is considered appropriate for powering a non-inferiority analysis in this natural experiment. In consultation with clinical experts, a non-inferiority margin (ΔNI) of 5% is deemed clinically acceptable to conclude that early surgery does not result in a clinically relevant increase in transfusion requirement. Non-inferiority will be demonstrated if the upper bound of the one-sided 95% confidence interval for the absolute risk difference between groups remains below 5%. Based on these assumptions, an expected event rate of 15% in the control group and 10% in the intervention group, with a one-sided alpha of 0.05 (Zα = 1.645) and a power of 90% (Zβ = 1.282), the required total sample size is 374 patients, with 187 per group.

As the sample size is based on the per-protocol population, patient inclusion will continue until 187 patients per treatment group have been included who adhered to the protocol of their respective school of treatment (Figure 2). Inclusion in a given school will stop once the required number of per-protocol patients (*n* = 187) is reached in that group. The other school will continue including patients until it also reaches the target of 187 per-protocol patients. As a result, the intention-to-treat population is expected to exceed 374 patients. Since the primary outcome is assessed during hospitalization, no loss to follow-up is anticipated. This approach provides sufficient power to robustly assess non-inferiority within the specified parameters.

### 5.8. Statistical Analysis

#### 5.8.1. Primary Outcome

The primary outcome is postoperative blood transfusion in hip fracture patients on DOACs. To assess non-inferiority of early surgery within 24 h compared to delayed surgery 24 h or more after last DOAC intake, the risk difference in transfusion requirement between both groups will be calculated with a corresponding one-sided 95% CI. Non-inferiority will be concluded if the upper bound of the one-sided 95% CI does not exceed the predefined non-inferiority margin of 5%.

In addition, a multivariable logistic regression analysis will be performed to estimate the adjusted odds ratio (aOR) and associated 95% CI for transfusion requirement, adjusting for potential confounders. Based on literature and expert-opinion, the following variables will be considered for inclusion in the regression model: sex, preoperative Hb, Clinical Frailty Scale, and type of surgical procedure [59,60,61,62]. Given a total sample size of 374 and an expected event rate of 15%, approximately 56 events are anticipated, allowing for inclusion of up to five independent variables, in accordance with standard rules to prevent model overfitting.

The primary analysis will follow a per-protocol approach, in which patients will be analyzed based on adherence to the surgical timing protocol of their respective hospital (i.e., within 24 h for School “A” centers and after 24 h or more for School “B” centers). Patients whose surgical timing deviates from this hospital protocol will be identified and excluded from the per-protocol analysis (Figure 2). In addition, an intention-to-treat (ITT) analysis will be conducted, in which patients will be analyzed according to the timing policy of their admitting hospital, regardless of actual timing. This ITT analysis will serve to assess the robustness of the findings, while preserving the effect of quasi-randomization and limiting the risk of confounding by indication. As a sensitivity analysis, propensity score matching will be applied to further assess robustness of the primary findings. This analysis will allow comparison of results obtained using propensity score matching with those derived from the natural experiment design and provide additional insight into the methodological value of the natural experiment approach.

Lastly, although we do not expect substantial inter-hospital variability, since all participating centers are Dutch level 2 trauma centers with similar hip fracture case volumes and resources, we will assess clustering by center using an intraclass correlation coefficient. If clustering of outcomes is detected (i.e., if some hospitals show greater similarity in outcomes than others), we will perform a multilevel logistic regression analysis to account for center-level effects. If no relevant clustering is found, the standard multivariable logistic regression will be deemed sufficient.

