## 1. Strengths and Limitations

This study addresses an urgent and clinically relevant knowledge gap regarding the optimal surgical timing for hip fracture patients on direct oral anticoagulants, with the potential to improve national and international guidelines.It utilizes a natural experiment design across seven Dutch trauma centers, leveraging existing practice variation to approximate randomization and enable real-world comparison of early surgery within 24 h versus delayed surgery 24 h or more after last direct oral anticoagulant intake, without interfering with routine clinical care, enhancing the generalizability of the findings.While the retrospective data extraction from electronic health records at predefined intervals is a limitation, all variables are prospectively predefined and standardized across participating hospitals, and regular data quality checks with structured feedback to centers are implemented to ensure consistency, completeness, and high data quality.Due to the limited number of covariates allowed in the regression model to prevent overfitting, there remains a risk of residual confounding; however, the most clinically relevant confounders will be accounted for in the analysis.A per-protocol primary analysis may be susceptible to confounding by indication; however, a pre-planned intention-to-treat analysis will assess the robustness of findings and mitigate this bias. In addition, time-dependent confounding cannot be fully excluded. Clinical or logistical factors arising during the preoperative waiting period, such as medical optimization, complications, or operating room availability, may influence both surgical timing and outcomes independent of direct oral anticoagulant status.

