## 3. Clinical Relevance

The findings of this study will be particularly significant for the hip fracture population for several reasons. There is currently no consensus on the optimal timing of surgery for hip fracture patients on DOACs, leading to considerable clinical practice variation in discontinuation protocols across The Netherlands [12,13,27,30,31]. Clear, evidence-based recommendations are urgently needed to standardize care and improve outcomes in this vulnerable and growing patient population [31,38].

If early surgery is shown to be non-inferior with respect to bleeding and thrombotic complications, this would support a paradigm shift toward performing hip fracture surgery within 24 h of last DOAC intake. This could lead to reduced hospital length of stay, faster mobilization and rehabilitation, and lower the risk of complications related to immobilization such as pressure ulcers and nosocomial infections [39,40]. Moreover, the reduction in HLOS could lead to significant cost savings for healthcare systems, as well as improved capacity and resource utilization [40,41].

If early surgery is proven inferior to delayed surgery, this study will help to define the optimal timing of surgery after DOAC discontinuation, possibly based on renal function and drug clearance. This could enable widespread (inter)national implementation of standardized perioperative protocols, ultimately contributing to evidence based, safe, and more efficient hip fracture care.

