## 4. Objectives

### 4.1. Primary Objective

To determine whether early surgery within 24 h after last DOAC intake compared with delayed surgery after 24 h or more results in a non-inferior blood transfusion risk in hip fracture patients on DOACs, where non-inferiority is defined as the upper bound of the one-sided 95% confidence interval for the absolute risk difference remaining below a predefined margin of 5%.

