## 5. Materials and Methods

### 5.1. Study Design

This cohort study is designed as a natural experiment and includes seven level 2 trauma centers across The Netherlands. Participating hospitals follow either an expert-based protocol permitting surgery within 24 h after the last DOAC intake or a conservative protocol requiring a minimum delay of 24 h. Patient inclusion starts in November 2025 and is expected to conclude in June 2027.

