#### 5.8.2. Secondary Outcomes

Secondary outcomes will be analyzed according to the type and distribution of each variable. Continuous variables (i.e., Hb decrease, bleeding index, surgery duration, time to DOAC restart, hospital length of stay) will first be assessed for normality using graphical methods (e.g., histograms). Normally distributed outcomes will be analyzed using parametric tests, specifically independent-sample t-tests. If the distribution is non-normal, non-parametric methods, such as the Mann–Whitney U test, will be applied. Ordinal or categorical variables with more than two categories, such as the number of packed red cell units transfused, will be analyzed using the Chi-square test. Binary outcomes, including thromboembolic events, postoperative complications, and a Hb decrease of more than 2 mmol/L, will be analyzed using Chi-square tests, or Fisher’s exact test in cases where expected cell counts are less than five.

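### Non-inferiority is decided on a risk difference with no stated adjustment between non-randomised per-protocol cohorts, and no adjusted risk difference is specified against the 5% margin

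*Protocol article*

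**What the plan says.** Section 5.1 of the protocol article describes the design: "This cohort study is designed as a natural experiment and includes seven level 2 trauma centers across The Netherlands". Allocation follows hospital policy.

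The primary objective (4.1) puts the margin on the absolute scale, with the "upper bound of the one-sided 95% confidence interval for the absolute risk difference remaining below a predefined margin of 5" percent. Section 5.8.1 gives the decision statistic, "the risk difference in transfusion requirement between both groups will be calculated with a corresponding one-sided 95% CI", and the rule: "Non-inferiority will be concluded if the upper bound of the one-sided 95% CI does not exceed the predefined non-inferiority margin of 5" percent. Neither section names a covariate, weight or standardisation step for that difference.

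Adjustment comes next, as a separate item: "In addition, a multivariable logistic regression analysis will be performed to estimate the adjusted odds ratio (aOR) and associated 95% CI for transfusion requirement". The candidate covariates are sex, preoperative Hb, Clinical Frailty Scale and type of procedure, within a stated limit of five variables. The multilevel model held in reserve for clustering is also logistic. Propensity score matching is planned as a sensitivity analysis, without an effect measure.

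The primary set is per-protocol, with an intention-to-treat analysis as a robustness check. Section 1 concedes that the per-protocol analysis may be open to confounding by indication. It also says that "the most clinically relevant confounders will be accounted for in the analysis".

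**The concern.** In a randomised trial, an unadjusted risk difference is an acceptable decision statistic. Here the groups are formed by which hospital a patient reaches, and then by removing patients whose timing departed from policy. Any net case-mix difference that remains goes into the number compared with 5%.

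Two features of the protocol make this more than a general caution:

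- Section 1 itself acknowledges possible confounding by indication in the per-protocol set.
- Section 5.2.2 describes one hospital where prosthesis surgery is delayed and other procedures are done early. In that hospital, procedure type determines timing, and 5.8.1 lists procedure type as a potential confounder. If its patients are divided between the cohorts by procedure, as that section implies, an imbalance in a listed confounder is built in.

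The adjusted odds ratio cannot settle the question, because no margin or reference risk is given on that scale. Under the rule as written, a crude difference that passes would be declared non-inferior even if the adjusted odds ratio pointed clearly the other way.

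**Working it through.** **1. The planned sample size.** Inputs from 5.7: 15% (delayed), 10% (early), margin 5 points, one-sided alpha 0.05 (1.645), power 90% (1.282).

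n per group = [0.15×0.85 + 0.10×0.90] × (1.645 + 1.282)² / (0.05 + 0.05)² = 0.2175 × 8.567 / 0.01 = 186.3, rounded up to 187.

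This reproduces the stated 187 per group and 374 in total. The formula is the unadjusted two-sample one, which supports reading the decision statistic as a crude difference.

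**2. Can the odds ratio be read against 5 points?** The odds ratio equivalent to +5 points depends on the control risk p: OR = [(p+0.05)/(0.95−p)] / [p/(1−p)].

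| Control risk | OR equal to +5 points |
|---|---|
| 5% | 2.11 |
| 10% | 1.59 |
| 15% | 1.42 |
| 20% | 1.33 |
| 25% | 1.29 |

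Conversely, an OR of 1.5 is +4.3 points at a control risk of 10% (inside the margin) and +5.9 points at 15% (outside). Without a reference risk or a standardisation step, the adjusted result has no fixed relation to the margin.

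**3. False non-inferiority under bias favouring early surgery.** Bias sizes are assumptions. Take a true difference at the margin, 20% v 15%, with 187 per group.

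SE = √[(0.16 + 0.1275)/187] = 0.0392; P(declare non-inferiority) = Φ(bias/SE − 1.645).

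- no bias: 5.0%
- 1 point: Φ(−1.390) = 8.2%
- 2 points: Φ(−1.135) = 12.8%
- 3 points: Φ(−0.880) = 18.9%

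If the variance follows the shifted early-surgery rate, the last three become 8.3%, 13.1% and 19.7%.

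**4. Power under bias against early surgery.** Start from the planning rates, 10% v 15%. With an observed early rate of 10%, 11%, 12% or 13%, power = Φ((0.05 − observed difference)/SE − 1.645), with SE recomputed each time: 90.1%, 82.8%, 73.3% and 62.0%.

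**5. How 3 points could arise.** For a binary confounder, bias = risk gap × prevalence imbalance. A 15-point gap and a 20-point imbalance give 0.15 × 0.20 = 3 points. Both values are assumed.

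**6. Does adjustment on the risk-difference scale work at this size?** Simulation with 2,000 runs, 187 per group, a true difference of +5 points in each stratum, and an assumed binary confounder with control risks of 10% and 25%:

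| Confounder prevalence, early / delayed | False non-inferiority, crude | False non-inferiority, standardised from logistic model |
|---|---|---|
| 50% / 50% | 4.8% | 4.9% |
| 40% / 60% | 17.6% | 4.4% |
| 35% / 65% | 30.7% | 5.3% |

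With the confounder measured, a standardised risk difference keeps the error near 5% and can be compared directly with the margin.

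**7. Event budget.** At the planning rates, expected events are 187×0.15 + 187×0.10 = 46.75, about 47. The protocol's figure of about 56 is 374×0.15, which applies the control rate to both groups. Four covariates plus treatment make five terms, or 46.75/5 = 9.4 events per term (56/5 = 11.2 on the protocol's count). An outcome model with many more covariates would break the protocol's own limit.

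**The case against.** The strongest defence is the design. Sections 5.2.1 to 5.2.3 argue that patients reach comparable level 2 centres for reasons unrelated to their characteristics, so a crude contrast approximates a randomised one. An intention-to-treat analysis is there to limit confounding by indication. That is a fair argument for small between-hospital bias. It does not cover the per-protocol exclusions or the hospital where timing follows procedure, and the intention-to-treat result has no stated adjustment for its risk difference either. Section 5.2.1 itself allows for residual confounding.

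The protocol also never uses the word crude, and a fuller analysis plan could specify adjustment. So crude is an inference. It rests on the decision rule being written out in full with no adjustment, on the adjusted model being presented as an extra, and on the sample size formula.

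Several stronger readings are tempting but not supported:

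- **That the odds ratio is the only adjusted result.** Propensity score matching is also planned, and it could yield a matched risk difference. The gap is that its effect measure and role are not stated.
- **That Section 1 contradicts 5.8.1.** The clause on accounting for confounders completes a sentence about the covariate limit in the regression model and concedes residual confounding. It does not claim that the margin comparison is adjusted.
- **That leaving out age, eGFR, DOAC type or antiplatelet use is an error.** The short list follows from a disclosed limit on model size, and its justification lies in sources not at hand.
- **That the secondary analyses are defective.** They use simple tests ("Normally distributed outcomes will be analyzed using parametric tests, specifically independent-sample t-tests"), but carry no decision rule.

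**Conclusion.** The point holds in this form: the number that decides non-inferiority has no stated adjustment, and nothing in the plan puts an adjusted risk difference against 5%. Because this governs the primary conclusion, it should be corrected before outcomes are compared.

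The documents do not show that confounding is present, how large it is, or which way it runs. A reader might infer that the crude comparison must favour early surgery; nothing supports that. If bias of 1 to 3 points favours early surgery, the nominal 5% error at the margin becomes about 8% to 19%. If it runs the other way, power at the planning rates falls from 90% to between about 83% and 62%. These figures rest on assumed bias sizes, the normal approximation, and 187 independent patients per group.

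A minor wording matter goes with this. Section 3 looks ahead to a result in these terms: "If early surgery is shown to be non-inferior with respect to bleeding and thrombotic complications". The objective in 4.1 confines non-inferiority to transfusion, and thrombotic outcomes have no margin. This is a loose phrase in a narrative section, not a second planned non-inferiority test.

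**What to change.** Make the decision statistic in 5.8.1 an adjusted marginal risk difference, compare its one-sided 95% upper bound with 5%, and report the crude difference as supportive. Choose one route in advance:

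- **Standardisation from the planned logistic model**, with sex, preoperative Hb, Clinical Frailty Scale, procedure as arthroplasty v fixation, and treatment. Entered as single terms, these make five and stay within the protocol's limit.
- **Propensity weighting**, which models cohort membership and so is not limited by the number of transfusions. It can take further collected covariates such as age, eGFR, DOAC type and antiplatelet use.

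Apply the same estimator to the intention-to-treat set. State the effect measure of the matched sensitivity analysis, preferably a risk difference. In Section 3, limit the non-inferiority wording to transfusion.

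The cost is a change of analysis text, some extra modelling and possibly a slightly wider interval. All the variables are already listed for collection in 5.4.

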## 2. Introduction

Early surgical intervention is the standard of care for hip fractures, and there is robust evidence that shorter time to surgery improves patient outcomes, whereas delays are associated with higher mortality and worse outcomes, including prolonged immobility, extended hospital length of stay (HLOS), and greater patient discomfort [1,2,3,4,5,6,7,8]. However, in hip fracture patients on direct oral anticoagulants (DOACs), surgery is often postponed due to concerns about increased intraoperative bleeding risk while the anticoagulant is still active [9,10,11]. Although reversal agents for DOACs such as idarucizumab and andexanet alfa are now available, their high cost has limited their widespread adoption [12,13]. 

The clinical importance of this dilemma is particularly relevant given that hip fractures are among the most common causes of hospital admission in older patients and are associated with high mortality and a loss of independence [14]. Nationwide registry data indicate that nearly 20,000 hip fractures occur annually in The Netherlands [15]. Hip fracture patients frequently have multiple comorbidities and cognitive disorders, further increasing their vulnerability to poor outcomes [16,17,18]. Cardiovascular disease requiring long-term anticoagulation is particularly common, and DOACs have largely replaced vitamin K antagonists and heparins due to their predictable pharmacokinetics, fixed dosing, and limited monitoring requirements [19,20,21,22,23,24,25,26]. Currently, 12–16% of hip fracture patients require long-term anticoagulation with DOACs [19,20,21]. DOACs target different sites in the coagulation cascade, either as direct factor Xa inhibitors (apixaban, edoxaban, rivaroxaban) or as a direct factor IIa inhibitor (dabigatran) [27]. Their half-life is typically 10–14 h but may be prolonged up to 27 h in older patients due to reduced renal clearance and altered distribution, adding further uncertainty on surgical timing decisions (Appendix A; Table A1) [27,28]. This is particularly relevant for dabigatran, which is predominantly cleared renally [27,28].

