Despite its clinical relevance, no consensus exists in the literature on the optimal surgical timing after DOAC discontinuation in hip fracture patients [12,27,29]. The uncertainty about this dilemma is reflected in clinical practice: 74% of surgeons consider current guidelines for hip fracture patients on DOACs inadequate, contributing to substantial clinical practice variation across hospitals [12,13,30,31]. Consequently, some hospitals postpone surgery for at least 48 h to mitigate bleeding risk, and some determine the timing of surgery based on renal function [12,13,30]. Retrospective studies suggest that early surgery may be safe; however, only one single-center study has directly compared the outcome of surgery performed within 24 h to after 24 h or more [27,32,33,34]. Nonetheless, expert consensus in several Dutch hospitals now permits immediate surgery for hip fracture patients on DOACs, as concerns also extend to preoperative blood loss from ongoing bleeding in unstabilized fractures [35,36,37].

This study will evaluate whether surgery within 24 h after last DOAC intake is as safe as surgery after 24 h or more in hip fracture patients on DOACs with respect to bleeding risk. Postoperative blood transfusion was chosen as the primary outcome because it represents a clinically relevant and objectively recorded outcome in routine practice. The hypothesis is that early surgery within 24 h results in a non-inferior postoperative blood transfusion risk compared to delayed surgery 24 h or more after last DOAC intake in hip fracture patients on DOACs. This protocol article outlines the design and methodological rationale of a natural experiment.

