### 5.4. Baseline Characteristics

The following baseline characteristics will be collected: age, sex, preoperative estimated glomerular filtration rate (eGFR in mL/min/1.73 m^2^), preoperative hemoglobin (Hb in mmol/L), preoperative hematocrit (Ht in L/L), type of DOAC (apixaban, edoxaban, rivaroxaban, or dabigatran), DOAC dosage, DOAC indication, hours since last DOAC intake, concurrent use of antiplatelet medication (yes/no), and the specific type of concurrent antiplatelet or anticoagulant medication used. Frailty indicators include a prior diagnosis of dementia (by a geriatrician or general practitioner), Body Mass Index (BMI in kg/m^2^), Short Nutritional Assessment Questionnaire (SNAQ) score, Clinical Frailty Scale (CFS), Charlson Comorbidity Index (CCI), American Society of Anesthesiologists (ASA) score, number of daily medications, pre-fracture living situation (independently at home, with assistance in Activities of Daily Living (ADL), or in institutional care facility), household composition (living alone, with a partner, or with family), pre-fracture mobility (based on the Fracture Mobility Score), and Katz-6 ADL score [47,48,49,50,51,52]. Fracture characteristics include the type of fracture (based on AO/OTA classification) and the surgical procedure performed (hemiarthroplasty, total hip arthroplasty, intramedullary nail, sliding hip screw, or cannulated hip screw) [46]. Lastly, the type of anesthesia (general or spinal), any preoperative use of tranexamic acid, fibrinogen, or platelet concentrates, and DOAC reversal agents (idarucizumab or andexanet alfa) will be registered. In addition, patients whose surgery was delayed for reasons unrelated to DOAC use will be documented, along with the specific reason for the delay. Measurement of DOAC plasma levels is not part of routine care in the participating centers and is therefore not included.

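### The covariates named for the adjusted model omit renal function and DOAC agent, which the protocol itself links to residual anticoagulant effect and, for renal function, to surgical timing

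*Protocol article*

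**What the plan says.** Section 5.8.1 plans a multivariable logistic regression alongside the risk difference. For its covariates, "the following variables will be considered for inclusion in the regression model: sex, preoperative Hb, Clinical Frailty Scale, and type of surgical procedure". The length of the list is justified by an event count: "Given a total sample size of 374 and an expected event rate of 15" percent, "approximately 56 events are anticipated, allowing for inclusion of up to five independent variables".

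Elsewhere the protocol gives renal function and agent a central place:

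- Section 2 says that DOAC half-life "may be prolonged up to 27 h in older patients due to reduced renal clearance and altered distribution, adding further uncertainty on surgical timing decisions", and singles out dabigatran as mainly renally cleared.
- Section 2 also reports of hospital practice that "some determine the timing of surgery based on renal function".
- Section 3 says that, should early surgery prove inferior, the best timing might be based on renal function and drug clearance.
- Table A1 gives renal clearance from about 27% (apixaban) to about 80% (dabigatran).
- Section 5.4 collects eGFR, together with "type of DOAC (apixaban, edoxaban, rivaroxaban, or dabigatran), DOAC dosage, DOAC indication, hours since last DOAC intake, concurrent use of antiplatelet medication (yes/no"). It also says that plasma levels are not included.

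Section 1 accepts some residual confounding because the model must stay small, but asserts that the confounders of greatest clinical relevance are covered. Section 5.8.1 also plans a supplementary intention-to-treat analysis and a propensity-matched sensitivity analysis. The article does not name the matching covariates.

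**The concern.** The clinical question is whether drug still active at surgery raises transfusion. Plasma levels are not measured, so eGFR and agent are the main recorded proxies for residual effect beyond the hours since last intake. By the protocol's own account, renal function can bear on both the timing of surgery and the bleeding risk, which makes it a plausible confounder. The named model has no term for it.

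The primary analysis set sharpens the point. Per-protocol membership depends on when surgery actually took place. A School A patient with poor clearance who is held beyond 24 h is excluded, while the same patient in School B stays in. Balance that arises from hospital allocation does not protect a set selected after allocation. If such exclusions happen, the remaining School A patients clear the drug faster on average, their transfusion rate falls, and early surgery looks safer than it is. The adjusted odds ratio, which readers will take as the check on confounding, would correct for this only as far as eGFR correlates with sex, Hb, frailty or procedure.

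**Working it through.** **1. The plan's own figures.** Section 5.7 assumes "an expected event rate of 15% in the control group and 10% in the intervention group", one-sided alpha 0.05, 90% power and a 5-point margin.

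- n per group = (0.15×0.85 + 0.10×0.90) × (1.645 + 1.282)² / (0.05 + 0.05)² = 186.3, so 187 per group and 374 in total. This reproduces.
- Events: 374 × 0.15 = 56.1, which reproduces the 56. It applies the delayed-group rate to both groups.
- With the two planning rates: 187×0.15 + 187×0.10 = 46.75, about 47 events.
- At 10 events per variable (my inference; the article refers only to standard rules), the budget is 5.6 terms at 56 events and 4.7 at 47.

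**2. Why renal function matters on the protocol's half-lives.** Assuming simple exponential decline, the fraction left at 24 h is 0.5^(24/half-life):

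- 10 h: 0.19
- 14 h: 0.30
- 27 h: 0.54

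**3. Size of the per-protocol selection.** The following are assumptions, not document figures: 30% of patients have low eGFR; their transfusion risk is RR times that of the others; average risk is 15%; there is no true timing effect; and a fraction x of low-eGFR School A patients is excluded and nobody else.

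- Risk in patients without low eGFR: r = 0.15 / (0.7 + 0.3×RR)
- Low-eGFR share left in School A: p = 0.3(1−x) / [0.3(1−x) + 0.7]
- Shift in risk difference = r × (1 − p + p×RR) − 0.15

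If 5% of School A deviates and all of them have low eGFR, then x = 0.05/0.30 = 0.167 and p = 0.25/0.95 = 0.263:

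| RR | r | School A risk | Shift (points) |
|---|---|---|---|
| 1.5 | 0.1304 | 0.1476 | −0.24 |
| 2.0 | 0.1154 | 0.1457 | −0.43 |
| 2.5 | 0.1034 | 0.1443 | −0.57 |

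Larger values need more deviation:

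| RR | x | School A excluded (0.30×x) | Shift (points) |
|---|---|---|---|
| 1.5 | 0.3 | 9% | −0.45 |
| 2.0 | 0.5 | 15% | −1.43 |
| 2.5 | 0.7 | 21% | −2.89 |

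**4. Cross-check with a different set-up.** Take one omitted binary factor, present in 25% of the delayed and 20% of the early cohort, with delayed risk 15% and no true effect. The shift is −0.28, −0.49 and −0.80 points at odds ratios 1.5, 2 and 3. The sign reverses if the imbalance runs the other way.

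**5. Model size** (degrees of freedom include the cohort term; frailty scale as one term).

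| Model | df | Events per df at 56.1 | Events per df at 46.75 |
|---|---|---|---|
| As listed, procedure in its five recorded categories | 8 | 7.0 | 5.8 |
| As listed, procedure binary | 5 | 11.2 | 9.4 |
| Procedure binary, plus eGFR | 6 | 9.4 | 7.8 |
| Procedure binary, plus eGFR, antiplatelet use and binary agent | 8 | 7.0 | 5.8 |
| Procedure in five categories, plus eGFR, antiplatelet use and four-category agent | 13 | 4.3 | 3.6 |

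**The case against.** A fair defence has several parts.

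- **The selection is not documented for these hospitals.** The remark about timing by renal function describes hospitals in general. Section 5.2.2 gives School A a standing policy of early surgery, attributes allocation to institutional protocol alone, and calls deviations rare. This stands. The mechanism is plausible, since the same section allows for clinical reasons for deviation in School A, but its scale is assumed.
- **Other analyses address it in part.** The intention-to-treat analysis does not exclude on actual timing, so this selection does not arise there. The matching covariates are unstated and may include eGFR and agent. This stands too. A reader might infer that no planned analysis can correct for drug-exposure differences, but the documents support that only for the named logistic model.
- **The list is not final.** The variables are to be considered for inclusion, and they rest on cited sources that were not available for this review. That softens the point. It does not explain why variables the protocol stresses are missing from the list while Section 1 says the main confounders are covered.
- **Overfitting.** Adding eGFR, agent and antiplatelet use together breaks the five-variable rule in an ordinary logistic model. This is right, and it is why only eGFR is proposed for the regression.
- **Antiplatelet use does not drive DOAC exposure.** Correct. It is an independent bleeding factor and belongs in the matching model on that ground only.

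**Conclusion.** The omission is a matter of fact and sits badly with the protocol's own emphasis on renal clearance and agent. It leaves a plausible confounder out of the named adjusted model, in an analysis set where selection on actual timing could bring it into play.

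The size cannot be known from the documents. With 5% of School A deviating, all of them low-eGFR, and the other assumptions above, the shift is about −0.2 to −0.6 points, or roughly 5% to 11% of the margin (0.24/5 and 0.57/5). These are unadjusted figures: they give no credit for correlation between eGFR and the planned Hb and frailty terms, and the direction depends on slow clearers being the ones delayed.

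Two stronger readings are not supported. One is a bias approaching 3 points, which needs about 21% of School A excluded solely for low eGFR together with a risk ratio of 2.5, against a protocol that expects deviations to be rare. The other is that changing the covariates would protect the non-inferiority conclusion. That conclusion rests on a risk difference described without adjustment, so the change improves the adjusted and matched supporting analyses only. This is a cheap improvement, not a flaw that invalidates the design.

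**What to change.** 1. Add preoperative eGFR, as a continuous term, to the prespecified regression covariates.
2. Enter procedure as arthroplasty versus fixation to hold model size. This split matches the one that Section 5.2.2 describes for the hospital with a mixed protocol, so that contrast is kept.
3. Name eGFR, DOAC agent and antiplatelet use (the last as an independent bleeding factor) in the propensity score model.
4. Report the balance of these three variables by cohort.

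**Cost.** All variables are already collected, so only the analysis text changes. The regression gains one term, with about 47 to 56 events, and uses a coarser procedure variable. At 6 df it is smaller than the listed model with procedure in five categories (8 df). Counting the cohort term it has six terms, one above the stated five. If the rule counts covariates only, eGFR takes the fifth place. Putting all three variables into the regression would need penalisation or dropping a listed covariate; that is a real trade-off and is not proposed here.
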